### Outcomes and analysis

This study is non-interventional and does not include follow-up endpoints. The analyses will focus on: Descriptive analysis of demographic and clinical characteristics, and frailty prevalence; Causal learning to determine key factors contributing to frailty in elderly CKD; Predictive model construction and validation using machine-learning and causal frameworks; Simulation-based recommendation system, producing interpretable suggestions for targeted nutritional, psychological, and physical interventions.

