## Background

With population aging accelerating, CKD has emerged as a global health priority, affecting 8–16% of adults and up to nearly 40% of older adults [1, 2]. Frailty, defined as a state of reduced physiological reserve and resilience, is a frequent and severe CKD comorbidity, significantly worsening disability, hospitalization, and mortality [3–6]. Prevalence studies report frailty in 20–50% of older CKD populations [7], driven by metabolic derangements, inflammation, sarcopenia, and multimorbidity [8–10].

Frailty in CKD is clinically important yet potentially reversible [11–13]. Multicomponent interventions combining nutrition, exercise, and psychosocial support have demonstrated benefit, but personalized decision frameworks remain underdeveloped [14–17]. Current screening tools, such as Fried’s phenotype or the FRAIL scale, offer population-level risk estimation but limited mechanistic insight or individualized guidance [18–21].

Artificial-intelligence (AI) methods now offer novel avenues for precision frailty management [22–25], particularly through causal learning and knowledge distillation. However, in routine nephrology practice, non-clinical indices derived from comprehensive geriatric assessment are often unavailable because of resource and workforce constraints, highlighting the need for scalable modeling strategies that can operate under incomplete data conditions. Causal learning disentangles interdependent disease mechanisms, revealing modifiable determinants rather than mere associations [26–28]. Knowledge distillation enables translation from complex multimodal teacher models to lightweight “student” models deployable in clinical settings [29–31]. Applying these methods to CKD-related frailty may bridge data-driven discovery with explainable, clinically actionable models.

This study aims to integrate geriatric assessment with AI-based causal reasoning to (1) identify key frailty-related factors in elderly CKD, (2) develop predictive and interventional-support models using causal learning and model distillation, and (3) evaluate potential real-world clinical feasibility and applicability of the proposed framework.

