## Methods

### Study design

A multicenter bidirectional cohort study is being conducted from December 1, 2024, to December 31, 2028 (Fig. 1). Beijing Chaoyang Hospital serves as the coordinating center, with six participating sites across tertiary and community hospitals. Both retrospective data extraction and prospective recruitment will be employed to establish a bidirectional cohort integrating hospital and community populations. Ethical approval has been obtained from the Institutional Review Board of Beijing Chaoyang Hospital (No. 2024-Science-914). All participants will provide written informed consent. The trial adheres to the Declaration of Helsinki and SPIRIT 2023 guidelines.

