### Recruitment and data collection

This is a multicenter, bidirectional cohort study. Eligible participants will be consecutively enrolled from nephrology and internal medicine departments across seven hospitals in Beijing. Retrospective data extraction will be performed only at the coordinating center (Beijing Chaoyang Hospital), while all participating centers will contribute prospective data collection. Pre-admission and admission-related baseline data, including demographic, clinical, and laboratory characteristics, will be retrospectively extracted from the electronic medical records (EMRs) at the coordinating center for eligible historical cases, while baseline standardized assessments will be prospectively performed at hospital admission for newly enrolled participants across all participating centers starting on January 3, 2025. During the prospective data collection phase, each participant will undergo standardized assessments encompassing: structured questionnaires for demographics, comorbidities, physical examinations and anthropometric measurements; laboratory tests including blood and urine biochemistry, inflammatory and metabolic indicators; geriatric assessment scales, frailty, cognition, nutrition, psychological state, physical performance. Collected variables were categorized into two groups: routinely available clinical indices (demographics, medical history, anthropometric measures and laboratory tests) and non-clinical indices, defined as non-routinely acquired geriatric assessment data (frailty scales and cognitive, functional, nutritional, and psychological assessments), which require specialized evaluation and are resource-intensive in routine clinical practice. All data will be entered into a harmonized electronic case-report form (eCRF). The database will be centrally curated at Beijing Chaoyang Hospital, following prespecified data quality control and harmonization procedures described below.

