### Statistical plan

Continuous variables will be presented as mean ± SD or median (IQR); categorical variables as frequency (%). Group comparisons will use Student’s *t* test, χ² test, or Mann–Whitney *U* test as appropriate. Causal effects will be estimated using do-calculus, counterfactual simulation, and feature-importance mapping. All analyses will be performed using R 4.3 and Python 3.11.

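### The causal analyses use patients recruited at hospital admission, so they are exposed to selection (collider) bias of unknown size and direction that the plan does not address

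*Protocol article*

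**What the plan says.** **Who enters.** Under Recruitment and data collection, participants are "consecutively enrolled from nephrology and internal medicine departments across seven hospitals in Beijing". In the prospective arm, "baseline standardized assessments will be prospectively performed at hospital admission for newly enrolled participants across all participating centers". In the retrospective arm, at the coordinating center only, "Pre-admission and admission-related baseline data, including demographic, clinical, and laboratory characteristics, will be retrospectively extracted" from the electronic records. Both arms are therefore organised around an admission.

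**A conflicting statement.** Study design says the aim is to "establish a bidirectional cohort integrating hospital and community populations", with tertiary and community hospitals as sites. No section describes how a person who is not admitted would be recruited.

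**What the protocol says about frailty.** Background describes frailty as "significantly worsening disability, hospitalization, and mortality" and as "driven by metabolic derangements, inflammation, sarcopenia, and multimorbidity".

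**What is to be concluded.** Outcomes and analysis lists "Causal learning to determine key factors contributing to frailty in elderly CKD". The Statistical plan adds: "Causal effects will be estimated using do-calculus, counterfactual simulation, and feature-importance mapping". The same analyses feed suggestions for nutritional, psychological and physical interventions. There is no follow-up.

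**The concern.** If frailty raises the chance of admission, and a candidate cause raises it too, then admission is a common effect of both. Restricting the analysis to admitted people can create or alter an association between them that has no causal content. Roughly, some patients without the factor are in the sample because they are frail, and some who are not frail are there because of the factor. A harmful factor can then look weaker, neutral or even protective.

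This is separate from reverse causation, which concerns the direction of an arrow, and from generalisability, which concerns transport to other people. It can arise for a factor that has no effect at all, and a larger sample does not remove it.

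At stake are the factors reported as contributing to frailty and the intervention suggestions built on them. Do-calculus identifies effects relative to a graph, so a graph that omits a selection step on which the data are conditioned can return a biased effect that appears identified.

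Nothing described in the article would reveal the problem. The six external validation centers also assess at admission. AUC, calibration, Brier score and decision curves test prediction, not causal validity. Multiple imputation deals with missing values among those enrolled. The limitations in the Discussion cover model drift, the inferred geriatric representations and center heterogeneity, but not selection by admission.

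**Working it through.** **Inputs from the protocol.** Both arms are tied to admission (Recruitment and data collection). Frailty raises hospitalization (Background, with no rate). The proposed drivers of frailty are illness-type factors (Background). That they also raise admission is an inference, reasonable for inflammation and multimorbidity but not stated.

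**The plan's own figures.** The sample size reproduces: 10 × 30 / 0.20 = 1,500, about 300 events, with a 95% half-width of 1.96 × √(0.2 × 0.8 / 1,500) = 2.02 percentage points. It is not in dispute and does not bear on this point. The protocol gives no admission rates, so everything below is an assumed range.

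**Formula.** For a binary factor X and frailty F, with admission probability depending only on these two:

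OR among admitted = population OR × [P(adm | both) × P(adm | neither)] / [P(adm | X only) × P(adm | F only)]

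The prevalences of X and F cancel.

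**Assumptions.** Baseline admission probability is 10%. X and F each raise admission 1.5-, 2- or 3-fold. Multiplier on the OR:

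| How the two effects combine | 1.5-fold | 2-fold | 3-fold |
|---|---|---|---|
| Multiply on the risk scale | 1.00 | 1.00 | 1.00 |
| Multiply on the odds scale (logistic) | 0.98 | 0.93 | 0.80 |
| Add on the risk scale | 0.89 | 0.75 | 0.56 |

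The 3-fold column in full:

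- Risk-multiplicative: 10/30/30/90% gives 0.90 × 0.10 / (0.30 × 0.30) = 1.00.
- Odds-multiplicative: odds of 1/9, 1/3, 1/3 and 1 are 10/25/25/50%, giving 0.50 × 0.10 / (0.25 × 0.25) = 0.80.
- Additive: 10/30/30/50% gives 0.50 × 0.10 / (0.30 × 0.30) = 0.56.

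**Baseline rate.** With 3-fold odds effects and a baseline of 5%, 10% or 20%, the multiplier is 0.86, 0.80 or 0.75.

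**Direction.** The multiplier exceeds 1 when the combined effect is stronger than multiplicative. With 10% for neither and 15% for each alone, the break-even for both is 0.15 × 0.15 / 0.10 = 22.5%. Above that, the OR is inflated.

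**Non-null effects (10% baseline).**

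- True OR 2.0: 1.60-1.96 (odds scale) and 1.11-1.78 (additive), so weakened but not reversed.
- True OR 1.5: 1.20-1.47 (odds scale) and 0.83-1.33 (additive). Reversal occurs only in the 3-fold additive case: 1.5 × 0.56 = 0.83.
- True OR 1.2: 0.96-1.18 (odds scale) and 0.67-1.07 (additive). Reversal occurs at 3-fold on the odds scale and at 2- and 3-fold when additive.

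**Would stratifying reveal it?** Suppose planned and unplanned admissions each had probabilities in the ratio 5/10/10/15. Each stratum would show 0.15 × 0.05 / (0.10 × 0.10) = 0.75 for a null factor. The strata agree perfectly on a spurious result, because each still conditions on admission.

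**The case against.** **Size is unknown, and may be nil.** This stands. If the two effects multiply exactly on the risk scale, the odds ratio is untouched. At 1.5- to 2-fold effects on the odds scale, a null moves only to 0.98-0.93. A reader might infer that the estimates are in fact biased, or that harmful factors will appear protective. The documents do not support that: they give no admission rates and link only frailty, not its candidate causes, to hospitalization. Exposure to bias is what can be shown.

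**Not everyone may be an inpatient.** A reader might take it as settled that every analysed patient was admitted. Recruitment and data collection points that way, but Study design speaks of community populations. What stands is a contradiction to be reconciled, with no non-admission route given.

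**Much of the work is not causal.** Also correct. The Background's first aim is to find frailty-related factors, and the primary analytical objective speaks of associations and prediction. It would be wrong to infer that the prediction model fails: among admitted patients it is not invalidated.

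**A condensed article need not specify the graph.** Partly fair. The discovery algorithm is not named, and it should not be assumed to be one that ignores selection. But the article itself fixes admission-based assessment and states an unhedged causal conclusion about older people with CKD. That combination is the problem, whatever algorithm is chosen.

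**Conclusion.** The point holds as one of exposure. With assessment in both arms tied to admission, and frailty acknowledged to raise hospitalization, the causal analyses in Outcomes and analysis and Statistical plan can be distorted by conditioning on admission. Neither the validation plan nor the stated limitations deal with this.

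Size and direction cannot be determined from the protocol. Under the assumed effects, a null OR appears as 1.0 (risk-multiplicative), about 0.75-0.98 (odds-multiplicative, across baselines of 5-20%) or about 0.56-0.89 (additive). Stronger-than-multiplicative selection would push it above 1. Reversal of a true effect needs a modest effect together with fairly strong, less-than-multiplicative selection.

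The conclusion rests on three assumptions: that admission-based entry is the operative rule, that a given candidate cause raises admission in its own right, and that the crude two-variable calculation is a fair guide. The second may not hold for every candidate. The conclusion reaches the causal claims and the suggestions derived from them.

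**What to change.** - **Reconcile the source population.** Make Study design and Recruitment and data collection agree. If people who are not admitted will be enrolled, describe the route; if not, remove the implication.
- **Show the selection.** In Causal-learning-based frailty modeling, Outcomes and analysis, and Statistical plan, include hospital admission in the graph as a conditioned-on selection node. The node makes the problem explicit; it does not by itself recover the effect.
- **Choose discovery accordingly.** Use a method that allows selection and latent common causes (FCI-type). Otherwise, do not interpret the learned edges causally.
- **Quantify.** Add a selection-bias analysis over a stated range of admission effects, covering additive, odds-multiplicative, risk-multiplicative and stronger-than-multiplicative forms.
- **Set the reporting rule.** Call a factor a determinant only if its effect is identified with the selection node present, or its direction survives the stated range. Otherwise report an association among admitted older patients with CKD.
- **State the limitation.** Add selection by admission to the limitations in the Discussion.

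Results by department, or by planned and unplanned admission if that is recorded, may be shown descriptively. Agreement across such strata must not be taken as evidence against the bias.

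The cost is analysis work and plan wording; none of these steps requires new recruitment. The downside is that fewer edges will be oriented and fewer factors can be called causal. With final analyses expected by mid-2028, there is time to prespecify this.

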### Statistical plan

Continuous variables will be presented as mean ± SD or median (IQR); categorical variables as frequency (%). Group comparisons will use Student’s *t* test, χ² test, or Mann–Whitney *U* test as appropriate. Causal effects will be estimated using do-calculus, counterfactual simulation, and feature-importance mapping. All analyses will be performed using R 4.3 and Python 3.11.

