### Multicenter quality assurance and data management plan

To ensure consistency across multiple centers and minimize heterogeneity, our research team implemented standardized procedures for assessment implementation, data collection, and quality control across all participating sites.

Unified Training and Standard Operating Procedures (SOPs): All investigators and research staff underwent centralized training before study initiation. This included detailed instructions on assessment implementation, data collection procedures, outcome assessment criteria and standardized delivery of multicomponent intervention recommendations across sites. Standardized assessment manuals and implementation checklists were distributed to each center, and regular online meetings were conducted to reinforce protocol adherence. A standardized case-report form (CRF) was developed and used uniformly across all sites to ensure consistent data recording.

Data Standardization and Quality Control: We established a multi-level data cleaning and quality control process. First, automated validation rules were embedded in the electronic data capture (EDC) system to check for completeness and logical consistency at the time of data entry. Second, centralized outlier detection and missing-data handling procedures were applied. Third, independent data verification was performed to ensure cross-field consistency and data integrity.

Centralized Data Management and Feedback Loop: A dedicated data management team was responsible for regular monitoring, data cleaning, and feedback to each participating center. Any discrepancies or missing data were promptly communicated to the sites for resolution, ensuring the reliability and completeness of the final dataset.

All procedures were conducted in accordance with the Guidelines for Data Management in Clinical Research, ensuring high-quality data to support subsequent modeling and analysis.

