### Measurements

#### Primary outcome

Frailty status in elderly CKD patients is defined using the FRAIL scale (Fatigue, Resistance, Ambulation, Illness, and Weight Loss; total score ≥ 3 indicating frailty). The primary analytical objective is to examine associations between clinical and non-clinical indices and frailty status and to support the development of individualized frailty risk prediction models.

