### Clinical workflow integration and deployment pathway

After model training and validation, the optimized student model will be integrated into an electronic medical record (EMR)–linked clinical decision-support interface. Routinely available clinical indices will be automatically extracted as model inputs. The system will generate individualized frailty risk scores and intervention suggestions, which will be presented to nephrologists and geriatricians through a structured dashboard. Model outputs will serve as assistive decision-support information, while final clinical decisions will remain under physician supervision, ensuring a human-in-the-loop implementation strategy.

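### Feature importance is listed as a causal-effect estimator, and for indices measured alongside FRAIL the design cannot separate causes of frailty from its consequences, yet intervention suggestions follow

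*Protocol article*

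**What the plan says.** All references are to the Protocol article.

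- **Estimators.** Statistical plan: "Causal effects will be estimated using do-calculus, counterfactual simulation, and feature-importance mapping".
- **Timing.** Recruitment and data collection: "baseline standardized assessments will be prospectively performed at hospital admission for newly enrolled participants". For historical cases at the coordinating center only: "Pre-admission and admission-related baseline data, including demographic, clinical, and laboratory characteristics, will be retrospectively extracted".
- **Outcome.** Primary outcome: current frailty status on the FRAIL scale, "total score ≥ 3 indicating frailty". The primary analytical objective is worded as association and support for risk prediction.
- **Follow-up.** Outcomes and analysis: "This study is non-interventional and does not include follow-up endpoints".
- **Causal claim.** The same section lists "Causal learning to determine key factors contributing to frailty in elderly CKD", together with a simulation-based system that suggests nutritional, psychological and physical interventions. The Background says that causal learning uncovers modifiable determinants and not only associations.
- **Deployment.** Clinical workflow integration and deployment pathway: "The system will generate individualized frailty risk scores and intervention suggestions". These go to nephrologists and geriatricians on a dashboard, under physician supervision.
- **Validation.** Validation and evaluation names AUC, calibration curve, Brier score and decision-curve analysis, with SHAP and causal-effect visualization for explainability.
- **Site training.** Multicenter quality assurance and data management plan: staff were trained in "standardized delivery of multicomponent intervention recommendations across sites".

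**The concern.** The plan moves from one occasion of measurement to causal effects, and from those to suggestions about what to change in a patient. Poor nutrition, low mood and poor function can each lead to frailty, and each can follow from it. When they are recorded at the same assessment as FRAIL, the data alone do not say which came first. These are also the domains that the suggestions target.

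Naming feature importance as a causal estimator adds a plain misstatement of method. A variable that is purely a consequence of frailty can be an excellent predictor of it and rank high in importance, although changing it would do nothing to frailty.

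At stake is what the study may conclude from its causal and intervention-support components, and what clinicians would be shown as levers. The frailty score itself is not in question.

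**Working it through.** The plan states no size for any causal effect, so there is no figure of its own to reproduce on this point. Its sample-size arithmetic (10 × 30 / 0.20 = 1,500, with 1,500 × 0.20 = 300 frail) reproduces and is not in dispute. Only the 20% prevalence is taken from it.

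**Step 1: timing, index by index.**

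| Index | When measured | Can it precede frailty status? |
|---|---|---|
| Age, sex, much of medical history | Before assessment by nature | Yes |
| Pre-admission records, coordinating center, historical cases | Before admission | Yes, for that subset |
| Nutritional, psychological, functional scales | Admission assessment | Not established |
| Admission laboratory values | Admission assessment | Not established |
| FRAIL status (outcome) | Admission assessment | n/a |

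**Step 2: what the named methods deliver.** Do-calculus takes a causal graph as given. Counterfactual simulation propagates a change along the arrows of that graph. Neither supplies the direction of an arrow between two quantities measured together; that must come from outside assumptions. Feature importance does not refer to an intervention at all.

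**Step 3: would the planned validation notice a reversed arrow?** A simulation used N = 1,500, prevalence 20%, one index X and 300 replicates per setting. X differs by d standard deviations between frail and non-frail (d is assumed). In world A, X causes frailty, with logit P(F) = ln(0.2/0.8) − d²/2 + d·X. In world B, frailty shifts X by d. The two worlds share one joint distribution by construction.

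| d | OR per unit X (A / B) | AUC (A / B) | Frailty after lowering X by 1 unit: A | B |
|---|---|---|---|---|
| 0.3 | 1.35 / 1.35 | 0.584 / 0.584 | 15.7% | 20% |
| 0.5 | 1.65 / 1.65 | 0.638 / 0.638 | 13.4% | 20% |
| 0.8 | 2.23 / 2.24 | 0.714 / 0.714 | 10.7% | 20% |

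The association reached p < 0.05 in 99% to 100% of replicates in both worlds. Metrics that depend only on the joint distribution of predictors and outcome, at the coordinating center or at the six partner centers, give the same answer in A and B. Only the effect of changing X differs.

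**Step 4: an illustrative size.** Assumed inputs: P(F) = 0.20 (the plan's prevalence); factor present in 40% of the non-frail; frailty causes the factor with odds ratio 2.0; the factor has no effect on frailty. The analyst draws the arrow from factor to frailty and does not adjust.

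- Odds of the factor in the frail: 2.0 × 0.40/0.60 = 1.333, so P(X|F) = 1.333/2.333 = 0.571.
- P(F|X) = 0.20 × 0.571 / (0.20 × 0.571 + 0.80 × 0.40) = 0.1143/0.4343 = 26.3%.
- P(F|no X) = 0.20 × 0.429 / (0.20 × 0.429 + 0.80 × 0.60) = 0.0857/0.5657 = 15.2%.
- Apparent gain from removing the factor: 11.2 points before rounding. True gain: 0.

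The same formulas with other assumed odds ratios:

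| Assumed OR | P(X\|F) | P(F\|X) | P(F\|no X) | Apparent gain | True gain |
|---|---|---|---|---|---|
| 1.5 | 0.500 | 0.1000/0.4200 = 23.8% | 0.1000/0.5800 = 17.2% | 6.6 points | 0 |
| 2.0 | 0.571 | 26.3% | 15.2% | 11.2 points | 0 |
| 3.0 | 0.667 | 0.1333/0.4533 = 29.4% | 0.0667/0.5467 = 12.2% | 17.2 points | 0 |

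**The case against.** The strongest reply is that the primary outcome, primary objective and performance metrics are associational and predictive, that the prediction model has internal and six-center external validation, and that outputs are assistive and under physician supervision. All of that stands and limits the consequence. It does not repair the causal wording, because a clinician cannot see a reversed arrow on a dashboard.

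The illustration can also be challenged. The odds ratio and the 40% are invented, and the apparent gain arises only if the arrow is drawn the wrong way without adjustment; drawn the right way, the same method returns zero. The two simulated worlds agree by construction. With many variables, structure learning can orient some arrows under added assumptions. These points are fair: the numbers show that the error is possible and would go unnoticed by the listed metrics, not that it will occur at that size.

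Stronger readings that a reader might infer are not supported:

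- *That the first aim cannot be answered.* The Background words it as identifying frailty-related factors, which one assessment can do. The causal wording appears in the Abstract and in Outcomes and analysis.
- *That the data hold no time order at all.* Demographics, medical history and pre-admission records at the coordinating center can precede frailty.
- *That reverse causation will be reported.* It could be; not every factor is a consequence of frailty.
- *That nothing is validated.* The score is. What is not described is any evaluation of the causal effects or the suggestions.
- *That a missing causal graph is itself an error.* An article may leave that to the full protocol or analysis plan.
- *That the study is in truth interventional.* The training text concerns recommendations, and an observational study can give advice without assigning treatment. The two statements need reconciling, no more.

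**Conclusion.** The point holds in this form. Feature-importance mapping is wrongly listed as an estimator of causal effects. For the geriatric scales and laboratory values taken at the same admission assessment as FRAIL, the design cannot separate cause from consequence without outside assumptions, so consequences of frailty could be presented as modifiable determinants and as intervention suggestions. The listed metrics assess frailty prediction only, and the limitations in the Discussion cover drift, inferred representations and center heterogeneity but not temporality or reverse causation.

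The size is not known from the documents. Under the assumed inputs above, the spurious gain is 6.6 to 17.2 percentage points for odds ratios of 1.5 to 3.0, against a true effect of zero. It vanishes at an odds ratio of 1 or when the arrow is drawn correctly. Demographics, medical history and pre-admission records are less affected, and the associational and predictive primary objective is not affected.

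**What to change.** 1. In Statistical plan, delete feature-importance mapping from the causal-effect estimators. Keep it under Validation and evaluation as model explanation.
2. State that causal-learning results for concurrently measured indices, and the simulated suggestions, are hypothesis-generating and not covered by the described validation. Limit the validated output to the frailty score.
3. Describe that score as the probability of prevalent frailty at assessment, so that risk is not read as the chance of becoming frail.
4. Add temporality and reverse causation to the limitations in the Discussion.
5. Reconcile the quality-assurance text on delivering intervention recommendations with the statement that the study is non-interventional.

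The cost is wording and narrower claims for the causal and intervention-support components. No new data, visits or participants are needed.
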